### Intervention

Both intervention arms will receive written smoking cessation materials and a series of 4 telephone-based counseling sessions and 1-3 in-person counseling sessions. Although the number, timing, and content of the counseling sessions will differ across the treatment arms, we anticipate that the total counseling contact time will be comparable, with one caveat. Participants in the SSC arm who are not interested in quitting within 30 days at the time of their baseline counseling session will not be offered additional counseling, which is consistent with most state quitlines. These participants will be informed that they may contact the program's hotline if they change their mind, at which point, counseling may either be reinstated or they will be referred to the state quit line for counseling. Participants in the SSC arm will receive 10 weeks of NRT contingent upon setting a quit date while participants in the LT-NRT arm will receive 52 weeks of NRT regardless of their immediate interest in quitting. An overview of the interventions is shown in Table 2.

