All participants in the LT-NRT arm will be asked to begin their NRT immediately after the baseline visit using the same dosing schedule outlined in Table 3. They will receive a 3-month supply of NRT at baseline and an additional 3-month supply after the Month 3, 6 and 9 counseling sessions. (*The timing of the resupply of medications mimics the 3 month medication supply typically used in healthcare settings for other chronic diseases – thus enhancing the potential for generalizability and adoption of the proposed intervention.*) The baseline visit will focus on the use of NRT, NRT adherence, and how NRT can be used to support smoking reduction. Smokers interested in making a quit attempt will be given cessation advice and supportive counseling as described in the written support materials. LT-NRT participants who continue to smoke will be asked to continue their NRT regardless of their current level of smoking and will be given supportive advice on maximizing adherence with NRT. LT-NRT participants who have quit smoking will be asked to continue NRT for a minimum of 6 months after they no longer experience smoking-related urges. If they have been abstinent for 6 months and no longer have urges to smoke, they will be provided a regimen for tapering their NRT dose with strict instructions for resuming the full dose if they have a slip or if smoking-related urges recur. LT-NRT participants will also receive adherence support counseling. Since some of the LT-NRT participants will not be ready for extensive counseling on quitting, the adherence support counseling will be particularly important. Adherence support counseling has been previously tested by our group and will assist participants in identifying problems remembering to take their medication and help them develop strategies for remembering (e.g., timing doses with routine activities of daily living, posting reminders, setting alarms). Adherence support counseling will reinforce the continued use of NRT as one of the single best strategies for quitting or reducing smoking. This counseling will follow a semi-structured format that assesses smoking status and medication use, probes for difficulties participants are having with their medication, assists participants in problem-solving around issues they are having remembering to take their medications, and offers suggestions for dealing with self-reported side effects. Notably this counseling approach has resulted in high rates of adherence to smoking cessation medication (86%, biochemically verified). In the present study, we will not be able to biochemically verify adherence to NRT since nicotine in the blood could reflect either adherence to the treatment or continued smoking. Instead, adherence will be assessed using a 3-day recall of medication use. This approach is considered the gold standard when biochemical verification of adherence is not possible and in our own work has been validated with high sensitivity and specificity against medication blood levels.

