### Analytical Plan.

**Sample Size and Power Calculations.** Our sample size was based on our primary outcome, point-prevalence abstinence at Month 12, using an intent-to-treat approach. Based on prior studies using precessation NRT, we estimate a 2-fold increase in cessation outcomes in the LT-NRT group compared to the SSC group. Given our recruitment of patients at all levels of readiness to quit, we estimate a 12 month cessation rate of 10%. With 199 participants, in each arm, we will have an 80% power to detect a 2-fold difference or greater with a Type I error rate of 5%. This sample size will provide comparable power for looking at 6 month sustained cessation. For the CO measured longitudinally at four time points, we have 80% power to detect a mean difference of 2.24 ppm. Likewise, for NNAL, we have 80% power to detect a mean difference of 0.41 pmol/mg creatinine or more between the two groups.

**Specific Aim 1: Compare the benefits of traditional smoking cessation (SSC) versus long-term guided maintenance therapy (LT-NRT) with NRT.** The chi-square test will be used to compare the verified 7-day point prevalence abstinence at Month 12 between the two groups. If there is imbalance between treatment groups at baseline, we will switch to logistic regression for our primary analysis. We will use similar methods to test for group differences for dichotomous secondary outcomes including sustained abstinence and proportion with 1 or more ED visits or hospitalizations. To test for differences in change in respiratory symptoms and FEV1 from baseline measured at 3, 6, and 12 months, we will use standard mixed models repeated measures analysis. Likewise, to test for differences in longitudinal exposure to CO and NNAL, we will compare the area under the curve over the entire 12 months of follow-up using repeated measures analysis. If the treatment differences are heterogeneous across any covariate sub-groups, we will quantify and report such interactions

with appropriate contrast statements. We will compare the cumulative number of self-reported quit attempts by means of a Wilcoxon rank-sum test.

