As smoking cessation trials are likely to have missing data, we will adopt the approach of Hedeker et al. for analyzing the primary binary outcome of smoking abstinence. We will initially conduct our analyses ignoring missing data and then conduct sensitivity analysis using three different approaches. The first approach will impute data under the two extreme assumptions of ‘missing = smoking’ and ‘missing = non-smoking’. The second approach will impute data using the last observation carried forward method, and finally we will conduct multiple imputations for missing data, modeling the uncertainty inherent in individual patient outcomes using a logistic regression model.

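### The sample size is set by intention-to-treat with no allowance for loss, but the lead analysis of the primary outcome leaves out participants whose outcome is missing

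*Protocol*

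**What the plan says.** All of this is in the protocol.

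- **Basis of the sample size** (Analytical Plan, Sample Size and Power Calculations): "Our sample size was based on our primary outcome, point-prevalence abstinence at Month 12, using an intent-to-treat approach".
- **Effect assumed** (same place): "we estimate a 2-fold increase in cessation outcomes in the LT-NRT group compared to the SSC group", and "we estimate a 12 month cessation rate of 10" per cent. The arm to which the 10% belongs is not named. Read as the standard smoking cessation (SSC) rate, it gives 10% v 20%.
- **Number and power** (same place): "With 199 participants, in each arm, we will have an 80% power to detect a 2-fold difference or greater". The type I error is set at 5%. The Study design section enrols the same 199 per arm.
- **Primary test** (Analytical Plan, Specific Aim 1): a chi-square test of verified 7-day abstinence at Month 12, with logistic regression if the arms are unbalanced at baseline.
- **Missing data** (Specific Aim 1, closing paragraph): the plan says that missing data are likely in trials of this kind, and continues "We will initially conduct our analyses ignoring missing data and then conduct sensitivity analysis using three different approaches". The three approaches are the two extreme imputations (all missing smoking, all missing not smoking), last observation carried forward, and multiple imputation.

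The protocol gives no expected loss rate and no inflation of the sample size. It does not say that a participant without a Month 12 outcome counts as a smoker in the main analysis.

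**The concern.** The two paragraphs describe different analyses. The sample-size paragraph commits to intention-to-treat. The missing-data paragraph leads with an analysis that omits anyone without a Month 12 outcome, and gives the label of sensitivity analysis to every approach that retains them. A reader cannot tell from the protocol which result decides the trial, and on the plain wording it is the complete-case one.

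Two things are at stake. First, the stated 80% power has no margin for loss, so whether it applies to the lead analysis depends on what the 10% and 20% refer to, which the plan does not say. Second, a complete-case comparison no longer compares the groups as randomised, and it can be biased if the chance of being seen at Month 12 depends on smoking status and does so differently in the two arms. The planned sensitivity analyses may then disagree with the lead result, and choosing among them after the data are seen would not be convincing.

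**Working it through.** **Inputs from the protocol:** 199 per arm, 10% v 20%, 5% type I error, 80% power, chi-square test. **Assumed, because the protocol gives none:** a two-sided test, loss of 10%, 20% or 30%, and the retention rates in step 5.

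**1. Reproduce the plan's figure.** Pooled-variance formula for two proportions, without continuity correction, with p̄ = 0.15:

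n = [1.960 × √(2 × 0.15 × 0.85) + 0.842 × √(0.10 × 0.90 + 0.20 × 0.80)]² / (0.20 − 0.10)²

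= (0.990 + 0.421)² / 0.01 = 198.96, so 199 per arm.

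Power at 199 per arm is 80.0%. The stated number is correct, and it contains no allowance for loss.

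**2. Complete-case power if 10% v 20% holds among those analysed.** With equal loss d, the number analysed per arm is 199 × (1 − d), and

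power = Φ{[0.10 − 1.960 × √(2 × 0.15 × 0.85 / n)] / √(0.25 / n)}.

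| Assumed loss | n per arm | Power |
|---|---|---|
| 10% | 179 | 75.7% |
| 20% | 159 | 70.6% |
| 30% | 139 | 64.7% |

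**3. The same reading, all 199 kept and missing counted as smoking.** The rates become 0.10 × (1 − d) and 0.20 × (1 − d). Power is 75.0% at 10% loss (9% v 18%) and 69.1% at 20% loss (8% v 16%). This is slightly below step 2, so the shortfall comes from the absent attrition allowance and not from the choice of missing-data rule.

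**4. Complete-case power if 10% v 20% are rates among all randomised, with missing counted as smoking and equal loss.** Rates among those seen rise to 0.10/(1 − d) and 0.20/(1 − d).

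| Assumed loss | Rates among those seen | Power |
|---|---|---|
| 10% | 11.1% v 22.2% | 80.8% |
| 20% | 12.5% v 25.0% | 81.8% |
| 30% | 14.3% v 28.6% | 83.1% |

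On this reading power is not lost.

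**5. Bias of the complete-case estimate.** Suppose that the rates among all randomised are 10% v 20% (ratio 2.0), that everyone missing is a smoker, and that retention differs by arm. The rate seen is the true rate divided by the retention.

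| Retained, SSC / LT-NRT | Seen, SSC v LT-NRT | Ratio |
|---|---|---|
| 80% / 90% | 12.5% v 22.2% | 1.78 |
| 85% / 70% | 11.8% v 28.6% | 2.43 |

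The error can run in either direction. With a true null of 10% in both arms, the same two patterns show 12.5% v 11.1% and 11.8% v 14.3%.

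**6. Counting missing as smoking is not free of bias either.** If 80% of SSC and 90% of LT-NRT are retained regardless of smoking status, the complete-case rates stay at 10% v 20%. Counting missing as smoking gives 8% v 18%, a ratio of 2.25.

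**The case against.** **On power.** A reader might infer that dropping missing outcomes is what forfeits the 80%. The figures do not support that. Steps 2 and 3 give nearly the same power for both rules, and step 4 shows no loss on a reading that the intention-to-treat wording allows. What stands is that the plan states neither an attrition assumption nor the population to which its rates apply.

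**On unequal retention.** A reader might also infer that retention will be better in LT-NRT. That arm receives "an additional 3-month supply after the Month 3, 6 and 9 counseling sessions", while SSC participants not interested in quitting within 30 days "at the time of their baseline counseling session will not be offered additional counseling". But counselling contact is not assessment contact. Under Study visits and data collection methods, both arms have the same assessments at 3, 6 and 12 months, with the same payment whatever the smoking status, plus transport help, reminders and flexible hours. The text ties no resupply to the Month 12 visit. Unequal retention is possible but is not shown, and its direction is unknown.

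**On the choice of method.** Step 6 shows that counting missing as smoking can itself favour one arm, so it cannot be presented as the only correct primary rule.

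**On what is already planned.** The plan foresees missing data and lists several analyses that keep everyone, so a discrepancy would show in the report. The word used for the complete-case analysis gives an order and does not literally say primary. This softens the point without removing it, because nothing else in the protocol is named as the main analysis and all the alternatives are called sensitivity analyses. Imputation predictors and arm-specific assumptions about the missing belong in a statistical analysis plan, and their absence here is no fault.

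**Conclusion.** The conflict is real. The trial is sized by intention-to-treat at exactly the number needed with no loss, while the lead analysis of the primary outcome ignores missing data that the plan expects. The arithmetic behind 199 is correct.

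The consequence for power is conditional. It is about 76%, 71% and 65% at assumed losses of 10%, 20% and 30% if 10% v 20% holds among those analysed, and about 81-83% if those are rates among all randomised with missing counted as smoking and loss equal by arm. On either reading the lead estimate is not intention-to-treat. It can be biased in either direction if loss depends on smoking status and differs by arm, but the documents do not show that this will happen.

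**What to change.** 1. Name one primary analysis that includes all 398 randomised participants (2 × 199) in their assigned arm, chosen from the methods already listed: multiple imputation, or missing counted as smoking. The choice between them is open to debate and should be made before outcome data are seen.
2. Move the analysis that ignores missing data to the sensitivity analyses.
3. State whether 10% and 20% are rates among all randomised or among those observed.
4. Restate power with an explicit attrition assumption. If they are rates among those observed, power is about 75-76% at 10% loss and 69-71% at 20%, where each range covers missing counted as smoking and complete cases.

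The cost is a few sentences and possibly a slightly less favourable power figure. No extra patients or data are needed.

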## Measures

**Outcome measures.** Our selection of outcomes was derived from scientific expert consensus and informed by input from our stakeholders and smokers with COPD. (Table 4) The primary outcome is biochemically verified 7-day point prevalence smoking abstinence defined as no cigarettes (not even a puff) for the previous 7 days at month 12. Biochemical validation will be based on expired CO, consistent with consensus statements from the Society for Research on Nicotine and Tobacco (SRNT). For those participants who have reported they have quit smoking and who are unable to be verified in this way, we will obtain verbal permission and contact information for a household member or other regular contact to provide proxy validation.

Secondary outcomes are 6 month sustained abstinence (biochemically verified), number of quit attempts, average CPD over the year of the study, and cumulative exposure to CO and NNAL. We will examine relapse rates 3 months after the conclusion of the study for participants who report they have quit smoking at the 12-month assessment. Clinical outcomes include both objective and subjective measures of respiratory function based on the measured FEV1 (as a percent of predicted) and the COPD Assessment Test.

We will also track both respiratory and cardiac clinical events. This will be done by self-report of intercurrent emergency department visits and hospitalizations at each follow-up visit. We will validate both the occurrence and the nature of these self-reported clinical events by blinded physician review of medical records.

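### The two extreme imputations for missing abstinence are extreme for each arm's quit rate but do not bound the difference between arms; arm-specific scenarios should be added

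*Protocol*

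**What the plan says.** Under Measures, the protocol states: "The primary outcome is biochemically verified 7-day point prevalence smoking abstinence", assessed at month 12. Under Analytical Plan, Specific Aim 1, the test is fixed: "The chi-square test will be used to compare the verified 7-day point prevalence abstinence at Month 12 between the two groups". Logistic regression takes over if the arms are imbalanced at baseline.

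The paragraph on missing data then sets the order of analysis: "We will initially conduct our analyses ignoring missing data and then conduct sensitivity analysis using three different approaches". Those sensitivity analyses are:

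- Extreme-case imputation: "The first approach will impute data under the two extreme assumptions of ‘missing = smoking’ and ‘missing = non-smoking"
- Carrying an earlier visit's status forward: "The second approach will impute data using the last observation carried forward method"
- Model-based imputation: "finally we will conduct multiple imputations for missing data, modeling the uncertainty inherent in individual patient outcomes using a logistic regression model"

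Only two extreme scenarios are named, and neither is distinguished by arm. The plain reading is one rule for every missing participant, although the text does not say so outright. The protocol expects missing data but gives no dropout rate.

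**The concern.** The quantity of interest is the difference in abstinence between LT-NRT and SSC. That difference is most sensitive to missing participants faring differently in the two arms. A rule that gives all missing participants the same status in both arms does not examine this. It moves both arms' rates together.

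A difference by arm among those lost is plausible here. LT-NRT participants have counseling through month 9 and NRT resupply through the year. SSC counseling ends at week 10, NRT depends on setting a quit date, and those not ready to quit at baseline are offered no further proactive counseling. Who is lost, and what they do afterwards, could differ between the arms.

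At stake is what the sensitivity section can support. A reader who sees two extremes reported will tend to take them as limits on the treatment effect. They are not.

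**Working it through.** **Inputs.** From the Analytical Plan: 199 per arm, 80% power, 5% type I error, a 10% cessation rate (read as the SSC rate) and a 2-fold effect, hence p0 = 0.10 and p1 = 0.20. Missing shares m1 (LT-NRT) and m0 (SSC) are assumptions: 10%, 20% and 30% in both arms, plus three unequal pairs. The planned rates are taken to hold among those observed.

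**The plan's own figure.** With pooled variance, two-sided 5% and 80% power:

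n = [1.96 × √(2 × 0.15 × 0.85) + 0.842 × √(0.10 × 0.90 + 0.20 × 0.80)]² / 0.10² = 199 per arm.

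This matches the protocol, so 10% v 20% is the planned contrast.

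**Formulas for the risk difference (RD).** If a fraction q of an arm's missing participants are abstinent, the arm's rate is (1 - m)p + mq. Therefore:

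- Missing = smoking in both arms: A = (1 - m1)p1 - (1 - m0)p0
- Missing = non-smoking in both arms: A + (m1 - m0)
- Crossed, worst for LT-NRT (its missing smoke, SSC's missing abstain): A - m0
- Crossed, best for LT-NRT (the reverse): A + m1

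The two planned rules span |m1 - m0| points. The possible range spans m1 + m0. With equal dropout the planned span is zero.

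**Results, RD in percentage points.**

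| Missing LT-NRT / SSC | Missing = smoking | Missing = non-smoking | Possible range |
|---|---|---|---|
| 10 / 10% | +9 | +9 | -1 to +19 |
| 20 / 20% | +8 | +8 | -12 to +28 |
| 30 / 30% | +7 | +7 | -23 to +37 |
| 15 / 25% | +9.5 | -0.5 | -15.5 to +24.5 |
| 25 / 15% | +6.5 | +16.5 | -8.5 to +31.5 |
| 10 / 30% | +11 | -9 | -19 to +21 |

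With equal dropout the observed-case difference of +10 points also lies outside the pair.

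**The planned test.** Uncorrected chi-square on whole counts, equal dropout:

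| Missing per arm | Missing = smoking | Missing = non-smoking |
|---|---|---|
| 10% | 36/199 v 18/199, OR 2.22, p = 0.008 | 56/199 v 38/199, OR 1.66, p = 0.034 |
| 20% | 32/199 v 16/199, OR 2.19, p = 0.014 | 72/199 v 56/199, OR 1.45, p = 0.086 |
| 30% | 28/199 v 14/199, OR 2.16, p = 0.022 | 88/199 v 74/199, OR 1.34, p = 0.153 |

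Using exact percentages instead of whole counts, 0.086 becomes 0.087. The RD is unchanged within each row. The p-value moves because both rates rise towards 50% and the variance grows, not because the arms have been allowed to differ.

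**Illustrative tipping point.** Let all missing LT-NRT participants smoke and a fraction q of missing SSC participants be abstinent. At 20% missing the rates are 0.16 and 0.08 + 0.2q.

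- q = 0.07: 0.160 v 0.094, z = 1.98
- q = 0.08: 0.160 v 0.096, z = 1.91

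Significance is lost at q = 8%, below the 10% assumed for observed SSC participants. At 10% and 30% missing the tipping values are 21% and 3%.

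**The case against.** Several points on the other side have force.

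- **The identity is narrow.** It concerns the risk difference with equal dropout. The planned test is a chi-square, and at 20% and 30% missing the two runs fall on opposite sides of 0.05. A reader might infer that the two analyses are redundant, or bound to agree and give false reassurance. The numbers do not support that: in these cases the plan as written would itself show some fragility.
- **Unequal dropout separates the two rules**, at 10%/30% even reversing the sign. This stands. But that spread comes from the imbalance in numbers lost, not from different quitting among those lost, and it is still smaller than the possible range.
- **Last observation carried forward uses each person's own last status**, so imputed rates can differ between the arms. It is therefore wrong to say that no planned analysis lets the arms differ. It does assume neither relapse nor late quitting after the last visit, and it does not vary that assumption deliberately.
- **The multiple imputation gets one clause**, and the protocol adopts the approach of a cited methods paper. Arm-specific terms may be set there or in an SAP. The criticism extends only to what the protocol describes.
- **The protocol never claims that the pair bounds the treatment effect**, and for each arm's rate the word extreme is correct. So this is no contradiction or misstatement.
- **The crossed bounds are limits, not forecasts.** They need every missing participant to quit in one arm and none in the other. The tipping-point result is the more useful one, and it too depends on assumed dropout.

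The protocol also plans retention measures, such as payment per assessment regardless of smoking status and transport help, so sensitivity analysis is not its only safeguard.

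**Conclusion.** The point holds in limited form. Applied uniformly, the two extreme assumptions do not bound the between-arm difference at any dropout level tried. Their risk differences coincide when dropout is equal and span only the gap between the arms' missing shares when it is not. With 40 points of possible range at an average of 20% missing, the planned pair covers 0 points at 20%/20%, 10 at 15%/25% and 20 at 10%/30%. Nothing else described in the protocol deliberately varies the outcome of missing participants by arm.

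Two stronger conclusions are not supported: that the missing-data plan as a whole fails, and that the existing analyses should be dropped. Removing missing = non-smoking or last observation carried forward would be a preference, not a correction.

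This rests on uniform application as the natural reading, on 10% v 20% among those observed, and on assumed dropout. It is an inexpensive improvement to one part of the sensitivity analysis.

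**What to change.** Keep all the planned analyses. In the missing-data paragraph of the Analytical Plan, add:

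1. The two crossed scenarios, labelled as outer bounds: LT-NRT missing = smoking with SSC missing = non-smoking, and the reverse.
2. An arm-specific tipping-point grid built on the planned multiple imputation. Vary the odds of abstinence in missing relative to observed participants separately in each arm, and report where the conclusion changes.

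It would also help to state that the two existing scenarios apply one rule to both arms and are extremes for the arm-specific rates only.

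The cost is a few lines of text and a little programming. The reported robustness may look less favourable.

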### **Matching patients with optimal treatment based on their own characteristics**

Our classification and regression tree (CART) analysis will allow us to provide more personalized recommendations for smokers with COPD and facilitate dissemination. CART is an analytical approach used as an alternative to logistic regression for the identification of subgroups of individuals who may have differential response to treatment. It can be used to develop a decision tree to guide clinical decision making. CART uses statistical methods to cluster individuals into different groups that have different outcomes related to the treatment. Using CART, multiple individual characteristics (e.g., gender, cigarettes

per day (cpd), cotinine level, readiness to quit, treatment assignment, etc.) can be considered simultaneously and variables can be identified that efficiently separate individuals into groups that are more or less likely to experience a positive outcome (e.g., abstinence). These variables can then be incorporated into a decision tree that will show the predicted outcome (response to treatment) based on a patient's given characteristics. The total number of splits or branches in the resulting decision tree depends on the number of critical variables identified in the CART analysis. The complexity of the decision tree can adapt itself to the complexity of the data. As a nonparametric approach, CART does not require specification of the nature of the relationship between predictors and outcome or a priori assumptions about the true model.

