**Specific Aim 2: Develop estimates of patient-desired outcomes based on patient-specific characteristics and treatment choice (SSC vs. LT-NRT)** We will employ a Classification and Regression Tree (CART) analysis to identify subgroups of participants whose personal characteristics might impact the benefit of treatment. The resulting decision tree will allow smokers and their care providers to estimate their individual chances of success given their choice of treatment. To maximize the utility of the decision tree, we will start by soliciting input from our Stakeholder Advisory Committee and Patient Advisory Panel. We will ask them to identify key demographic, psychosocial, biological, and smoking factors from Table 5 and help us convert them into clinically meaningful binary variables that could be tested for inclusion in a clinically meaningful decision tree. (Drs [name] and [name] will provide both groups with simple conceptual models to assist them in providing meaningful, independent contributions.) The candidate variables, along with treatment assignment (LT-NRT vs SC) will be entered into a recursive partitioning model as described by Brieman and Friedman using the RPART package in the R statistical software. Specific methods related to building the tree (using appropriate splitting criteria and loss incorporation using the altered priors method), pruning the tree and handling missing data (using surrogate variables) will be deployed using the techniques described by Therneau et al. Given the event rates expected and overall sample size, a validation subsampling scheme will not be feasible, thus we will utilize 10-fold cross-validation on the regression tree to assess its properties. Additionally, we will account for the uncertainty in tree classification by generating a bootstrap sampling distribution of the CART as described by Shalizi. In addition to developing a CART model/decision tree for smoking cessation, separate classification models will be developed for other high priority binary outcomes, including: 1) 6 month sustained abstinence; 2) 50% reduction in carcinogen (NNAL) exposure; and 3) COPD related hospitalization (yes/no). (These were the models of greatest interest for our initial Patient Advisory Panel, but other outcomes could be modeled as well if our patients and stakeholders think that these additional models might be useful.)

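### The Aim 2 tree enters treatment as one candidate split among many, so nothing guarantees that it yields the promised estimate for each treatment choice

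*Protocol*

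**What the plan says.** Protocol, Analytical Plan, Specific Aim 2: advisers choose factors from Table 5 and help turn them into binary variables. Then "The candidate variables, along with treatment assignment (LT-NRT vs SC) will be entered into a recursive partitioning model", fitted with RPART, "using appropriate splitting criteria and loss incorporation using the altered priors method", followed by pruning, 10-fold cross-validation and a bootstrap of the tree. The stated product is that "The resulting decision tree will allow smokers and their care providers to estimate their individual chances of success given their choice of treatment".

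The section on matching patients with optimal treatment lists treatment assignment as one characteristic among several. It presents the method as suited to the "identification of subgroups of individuals who may have differential response to treatment", but describes selection thus: "variables can be identified that efficiently separate individuals into groups that are more or less likely to experience a positive outcome". The same section goes on to promise any smoker with COPD an estimate for a specific treatment choice. The dissemination section puts the tree on the web and in the electronic health record.

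The protocol does not force a treatment split, grow a tree per arm, split on differences in treatment effect, or plan to report leaf rates by arm.

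**The concern.** The algorithm and the promise answer different questions. An outcome-splitting tree ranks candidates by how well they separate abstainers from smokers. Treatment competes with readiness to quit, dependence and the rest, and may be passed over or pruned away. Where that happens, the tree shows one figure for both treatments.

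Because the tree is a decision aid, its silence on treatment could be read as no difference between treatments, even if the trial's assumed two-fold effect is real. Aim 2 is one of two specific aims.

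**Working it through.** **1. The plan's own figure.** Inputs from the sample size paragraph: 199 patients per arm; "we will have an 80% power to detect a 2-fold difference or greater with a Type I error rate of 5" per cent; and "we estimate a 12 month cessation rate of 10" per cent, doubled to 20% under LT-NRT. With pooled variance, two-sided 5% and 80% power:

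n = [1.96·√(2·0.15·0.85) + 0.842·√(0.10·0.90 + 0.20·0.80)]² / 0.10² = (0.990 + 0.421)² / 0.01 ≈ 199 per arm. The figure reproduces.

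Expected abstainers: 199·0.10 ≈ 20 and 199·0.20 ≈ 40, so about 60 of 398 (15%). The protocol gives no figure for the tree.

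**2. What a branch without treatment shows.** With equal arms, its raw rate is the average of the two. At the planned rates, both choices would read (10% + 20%)/2 = 15%.

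**3. Relative strength of the candidates.** Treatment odds ratio (OR): (0.20/0.80)/(0.10/0.90) = 2.25. Covariate strength is an assumption. One scenario uses protocol figures: 7 of 21 interviewed smokers ready to quit, 80% failure among motivated smokers, and 10% overall. Solving (1/3)·20% + (2/3)·x = 10% gives x = 5%. The readiness OR is then (0.20/0.80)/(0.05/0.95) = 4.75. If the two-fold effect applies to everyone, LT-NRT becomes 40% v 10%, OR 6.0.

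**4. Simulation with RPART.** 398 patients, true rates 10% and 20%, 8 binary covariates of which one is prognostic (prevalence about 1/3), complexity parameter 0.01, 10-fold cross-validation, 400 to 500 trials per setting. The last row pools several runs with 8 or 15 covariates and 200 or more trials where the number was recorded; one used complexity parameter 0.001. Entries are the percentage of pruned trees that omit treatment (minimum error / 1-SE).

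| Prognostic covariate | Priors 0.5/0.5 | Priors 0.6/0.4 | Anova | Loss 4:1 |
|---|---|---|---|---|
| none (OR 1) | 8–9 / 13–17 | 59 / 88 | 58 / ~100 | 99 / 99 |
| OR 1.5 | 9 / 16 | not run | 57 / ~100 | ~100 |
| OR 2 | 21–22 / 32–33 | 45 / 76 | 61 / ~100 | ~100 |
| OR 2.5 | 33 / 44 | 46 / 71 | not run | not run |
| OR 3 | 51–53 / 65–66 | 37 / 64 | 62 / 97 | ~100 |
| OR 4 | 67–68 / 82–84 | 53 / 73 | 63 / 96 | ~100 |
| Readiness 20% v 5% | 78–84 / 93–96 | 54–62 / 80–81 | 56–63 / 93–94 | not run |

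Another run with no prognostic covariate gave 11 / 21 (balanced priors) and 63 / 88 (0.6/0.4). With readiness at 15% v 7.5% and balanced priors, omission was 30 / 44 in one run and 27 / 44 in another.

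**5. Presence in the tree is not enough.** Treatment must lie on every path. At OR 3 that held in 31% / 27% of trees with balanced priors, 23% / 14% with 0.6/0.4 priors, 16% / 1% with anova and about 0% with the 4:1 loss. With balanced priors, on average 40% / 31% of patients had treatment on their path.

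**6. When benefit differs by readiness** (balanced priors). With benefit only in non-ready smokers, 22% / 11% of trees contained treatment. With benefit mainly there (4% to 17%, against 22% to 26% in ready smokers), 71% / 57% did.

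**The case against.** A reader might infer that the tree will usually omit treatment and cannot give estimates by treatment choice. The documents do not support either.

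- **Usually.** Omission depends on covariate strength, priors or loss, and the pruning rule. The protocol gives no values for these and may properly leave them to the analysis plan. With balanced priors and an OR of 2.5 or less, most trees kept treatment. The 20% v 5% scenario is at the strong end. Its 80% failure rate is a general statement about motivated smokers, not verified 12-month abstinence in COPD, and 7 of 21 is a small interview sample.
- **Cannot.** Treatment is randomised, so any leaf can be tabulated by arm. The protocol already plans to calculate other outcomes for each branch, though it does not say by arm.
- **A prognostic covariate as the only cause.** Under 0.6/0.4 priors, anova or a loss matrix, treatment was mostly lost without one, because the tree often collapses to its root. With about 60 events, sparse data are part of the problem.

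Aim 1 also promises interaction contrasts where effects differ across subgroups, and the Aim 2 bootstrap would expose unstable treatment splits. Both are useful. But the contrasts do not feed the tree, and a bootstrap of a tree without treatment still gives no estimate by arm. The algorithm and the way treatment enters are fixed in the protocol, so the structural gap stands.

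**Conclusion.** The concern holds as a mismatch between method and aim. As specified, the pruned tree need not contain treatment on any path, and a branch without it predicts the same chance under both arms. With the planned effect true, the omission share runs from about 9% to 16% (covariate OR 1.5, balanced priors) to about 80% to 95% (readiness 20% v 5%, balanced priors), and to nearly 100% with a 4:1 loss. With 1-SE pruning and OR 3 or more, it was about 64% or higher in every setting run.

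These figures rest on assumed covariate number and strength and on assumed priors or losses. They cover abstinence only, not the trees planned for sustained abstinence, carcinogen reduction or hospitalisation. They show that the promised output is not assured, and do not predict which tree this trial will produce.

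**What to change.** In Specific Aim 2, keep treatment on every path by forcing it as the first split or growing one tree per arm. Each patient then has an estimate under each treatment by construction. At minimum, state that every terminal node's outcome rate will be reported by randomised arm, with the difference and a bootstrap interval. Label a plain RPART tree as prognostic wherever it is published.

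An interaction tree or model-based recursive partitioning is an option for the effect-modification question, not a requirement.

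The cost is analysis wording and freely available software, with no new data or patients. The downside is precision: with about 20 and 40 expected quitters in the two arms, leaf estimates by arm will be wide, and few or no effect-modifying splits may appear.
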